### Interventions

#### Standard care programme

Participants in the standard care programme (control group) will receive written and verbal information about their surgical procedure, described medications, and secondary prevention during the hospital stay at the surgical ward. The standard follow-up after discharge consists of two visits at the outpatient clinic (Fig. 3):
Visit 1: 4–8 weeks after revascularisation. The participant meets a vascular surgeon during 20 min.Visit 2: 1 year after revascularisation. The majority of the participants meet a vascular nurse during 30–40 min. Some participants with more complicated cases will meet a vascular surgeon during 20 min instead of a nurse, and this decision is made during visit 1.

**Fig. 3 Fig3:**
[figure not shown]
Description of outpatient visits and telephone calls with estimated time required for participants in the intervention group vs the control group

During these visits, the participants are managed following guideline-directed care^2^, which includes interval history (new symptoms) and vascular examination of the leg and the surgical site. A pharmaceutical review of the participant’s medical treatment is performed, and information of secondary preventive measures is supposed to be provided.

#### Intervention programme

Participants in the intervention programme (intervention group) are also managed following guideline-directed care [2], but will also receive a nurse-led, person-centred, health-promoting follow-up programme in accordance with the PCC approach described by Ekman et al. [17]. The vascular nurses in this programme (FASTIC nurses) are specially trained in PCC and in motivational interviewing (MI). MI is a method focused on helping patients adhere to treatment recommendations by exploring their personal perspectives and ambivalence, identifying barriers, and promoting behavioural changes [27]. A partnership between the participant and the FASTIC nurse is initiated at a meeting at the surgical ward before discharge. The following programme consists of three visits at the outpatient clinic and two telephone calls (Fig. 3). All contacts between the participant and the FASTIC nurse are based on the participant’s own narratives and a joint agreement on a self-care plan. The intervention programme includes some questions and reflections about the participant’s lifestyle. That could be experienced as intrusion by some participants. Therefore, all conducted dialogs will be based on the individual patient’s needs and wishes. The nurses will have regular meetings with the principal investigator to discuss methodology, approaches, and any issues that arise in the process.

##### **Participant narrative** (Fig. 4)

In a narrative, the participant describes their self-perceived health history, previous knowledge on the disease, risk factors, received treatment, and expectations of the future. Furthermore, the participant recounts their capabilities and limitations to meet their own self-care goals (e.g., behaviour/lifestyle changes and adherence to medications.

**Fig. 4 Fig4:**
[figure not shown]
The main content of the participants’ narrative

Based on the narrative, the FASTIC nurse and the participant discusses relevant information on the disease (arthrosclerosis), received surgical treatment, the increased risk for future cardiovascular and cerebrovascular events due to cardiovascular disease, available BMT, and modification of risk factors (smoking cessation, healthy diet, physical activity, and adherence to medication). The information from the nurse is provided by dialog using open-ended questions, reflective listening, and summary statements inspired by MI. Different methods (printed material, schematic pictures, and short films) are used if the participant needs specific information. Individualised advice and recommendations on lifestyle (diet, alcohol consumption, and physical exercise) are based on the European guidelines on cardiovascular disease prevention in clinical practice [28], the Swedish national guidelines for disease prevention methods [11], the Swedish national guidelines for physical activity in the prevention and treatment of disease [29] and Nordic nutrition recommendations [30].

##### Self-care plan

After summarising the narrative and the dialog described above, a joint agreement on a self-care plan is established and documented in the medical record. The self-care plan contains a detailed description on goals, strategies, the participant’s own capabilities to achieve the goals and the need of support from the FASTIC nurse. Examples of such support are referrals to expertise (e.g., for smoking cessation, physical therapy, contact with dieticians) or to primary care. The FASTIC nurse provides strategies to improve adherence to medications and to lifestyle changes. The written agreement of the self-care plan is provided to the participant either before discharge or sent by post within 1 week of discussion during the information session. During every contact between the participant and the FASTIC nurse, the self-care plan is reviewed and modified if required.

Because each participant has his/her own personalised self-care plan, there are no mandatory interventions. All interventions will be documented in the participant’s case report form and reported at the end of the study.

### Data collection

#### Biomarkers

Biomarkers will be measured at study enrolment and at 1 year after revascularisation. Blood samples will be collected to assess HbA1c, triglyceride, high- and low-density cholesterol, and total cholesterol levels. An exhalation test for measuring carbon monoxide, the piCO™ Smokerlyzer® (Bedfont® Scientific Ltd., Kent, England), will be used to assess smoking status.

#### Adherence to medication

The primary outcome, adherence to medication, is defined as adherence to prescribed antithrombotic agents and lipid modifying agents 1 year after revascularisation.

The Swedish Prescribed Drug Registry (PDR) will be used for collecting data on medication adherence. The PDR provides data on prescribed drugs containing information on dispensed items, dispensed amount, dosage, and expenditure. Furthermore, this registry has been linked to the civic registry number since 2005 and thus provides information on an individual basis. This registry does not include medications that are prescribed and administered in hospitals [31]. Data from a period of 18 months (6 months before to 12 months after revascularisation) will be retrieved from the PDR for each participant. The WHO Collaborating Centre for Drug Statistics Methodology classification of Anatomical Therapeutic Chemical (ATC) codes will be used to identify antithrombotic agents and lipid-modifying agents (see Table 1 for specific codes). Although antihypertensive medications will not be included in the analysis for primary outcome, they can be considered as BMT for patients with hypertension. Information on antihypertensives will be retrieved from the PDR as medication of interest for the study. We will also collect patient-reported adherence to medication (anticoagulant agents, antiplatelet agents and lipid-lowering agents) at study enrolment and at 1 year after revascularisation.

**Table 1 Tab1:** Medications of interest in the study

Medication group	ATC Code
Antithrombotic agents	
Vitamin K antagonists	B01AA
Heparin group	B01AB
Platelet aggregation inhibitors excluding heparin	B01AC
Direct thrombin inhibitors	B01AE
Direct factor Xa inhibitors	B01AF
Lipid-modifying agents	
HMG CoA reductase inhibitors	C10AA
Fibrates	C10AB
Other lipid-modifying agents	C10AX
Antihypertensives	
Diuretics	C03
Beta-blocking agents	C07
Calcium channel blockers	C08
ACE inhibitors, plain	C09A
ACE inhibitors, combinations	C09B
Angiotensin II antagonists, plain	C09C
Angiotensin II antagonists, combinations	C09D

legend: Medications of interest in the study and their Anatomical Therapeutic Chemical (ATC) codes according to the WHO Collaborating Centre for Drug Statistics Methodology (WHOCC) classification*.*

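### The lipid part of the primary outcome is defined on a whole drug class, but the Table 1 codes that identify it cover three subgroups and no combination group, so some treated patients could be missed

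*Protocol article*

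**What the plan says.** All the relevant text is in the protocol article, under Data collection, Adherence to medication, with Table 1.

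- **Outcome.** The primary outcome "is defined as adherence to prescribed antithrombotic agents and lipid modifying agents 1 year after revascularisation". The lipid class carries no restriction.
- **How the drugs are found.** Dispensing data come from the Swedish Prescribed Drug Registry, from 6 months before to 12 months after revascularisation. ATC codes "will be used to identify antithrombotic agents and lipid-modifying agents (see Table 1 for specific codes").
- **Lipid codes.** Table 1 has three rows: "HMG CoA reductase inhibitors C10AA", "Fibrates C10AB" and "Other lipid-modifying agents C10AX".
- **Combinations.** The table has separate rows for "ACE inhibitors, combinations" (C09B) and "Angiotensin II antagonists, combinations" (C09D). The same section says that antihypertensives do not enter the primary analysis. No combination row appears under lipid-modifying agents.
- **Scoring.** The article gives no rule for turning dispensings into adherent or non-adherent, and none for a switch to an unlisted product. It does not say whether Table 1 limits the registry extract.

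**The concern.** The stated outcome is wider than the code list that is meant to deliver it. This is not a detail left to another document: the article itself points to Table 1 for the codes. A patient whose lipid treatment is replaced entirely by a product outside the three subgroups would have no listed lipid dispensing from then on. Read through Table 1, that looks the same as a patient who stopped.

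The table's own layout suggests how this could happen. Its antihypertensive rows show that the classification can give combinations a code of their own, apart from the plain products. The antihypertensives are captured broadly (whole groups C03, C07 and C08, and both combination groups), while the lipid component of the primary outcome is captured only at the narrower five-character level.

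At stake is false non-adherence in the primary outcome: both observed adherence rates would be too low and the difference between arms too small. Patient-reported use of lipid-lowering agents is also collected at enrolment and 1 year and could reveal such patients, but nothing says that it corrects the registry result. The trial is unblinded (Randomisation), so the handling of unlisted products is better fixed before anyone examines the registry data by arm.

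**Working it through.** **Step 1: outcome against code list.**

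| Class | In primary outcome? | Rows in Table 1 | Combination row? |
|---|---|---|---|
| Lipid-modifying | Yes | C10AA, C10AB, C10AX | None |
| ACE inhibitors | No | C09A, C09B | Yes, C09B |
| Angiotensin II antagonists | No | C09C, C09D | Yes, C09D |

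All three lipid codes begin with C10A. "Other lipid-modifying agents" is a single five-character subgroup, and nothing says that it takes in combinations. The code list is therefore narrower than the named class, by an amount the article does not let one measure.

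**Step 2: reproduce the planned sample size.** Inputs from Sample size: 50% vs 70%, two-sided 0.05, power 0.80, stated total 186. A 1:1 allocation is assumed, since the ratio is not stated. With pooled variance and no continuity correction, and p̄ the mean of p1 and p2:

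n per arm = [1.960·√(2p̄(1−p̄)) + 0.8416·√(p1(1−p1) + p2(1−p2))]² / (p2−p1)²

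= [1.960·√0.48 + 0.8416·√0.46]² / 0.04 = (1.3579 + 0.5708)² / 0.04 = 93.0

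That gives 93 per arm and 186 in total, as stated. The recruitment target of 210 less 10% drop-out leaves 189, so there is almost no reserve.

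**Step 3: effect of missed patients.** Let m be the share of truly adherent patients whose only lipid product is unlisted and who are then scored as non-adherent. The article gives no value, so m is assumed. The observed rates become 0.5(1−m) and 0.7(1−m), and

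power = Φ{[(p2−p1)·√93 − 1.960·√(2p̄(1−p̄))] / √(p1(1−p1) + p2(1−p2))}

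For m = 2%: p1 = 0.490, p2 = 0.686, p̄ = 0.588. Power = Φ[(1.890 − 1.364)/0.682] = Φ(0.771) = 0.78.

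| m, equal in both arms (assumed) | Observed rates | Difference | Power at 93 per arm | Total N for 80% power |
|---|---|---|---|---|
| 0% | 50.0% vs 70.0% | 20.0 points | 0.80 | 186 |
| 1% | 49.5% vs 69.3% | 19.8 | 0.79 | 192 |
| 2% | 49.0% vs 68.6% | 19.6 | 0.78 | 196 |
| 5% | 47.5% vs 66.5% | 19.0 | 0.75 | 212 |
| 10% | 45.0% vs 63.0% | 18.0 | 0.70 | 240 |

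Equal loss leaves the ratio of the rates at 1.4 (70/50 = 63/45) and shrinks the difference.

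**Step 4: one-arm scenario.** If only intervention patients were affected, the comparison would be 50% against 0.7(1−m). Power would be 0.77, 0.74, 0.63 and 0.43 for m = 1%, 2%, 5% and 10%. This shows sensitivity and is not a forecast.

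**The case against.** The strongest reply is that the article shows a short code list but no harm. It names no lipid product outside the three codes and does not say that any participant uses one. The separate antihypertensive rows show that combinations can have their own codes, not that a lipid combination in use was left out. Table 1 mixes code levels throughout, so its layout may mean little. This stands as a limit on the size of the problem. It does not remove the mismatch between a class-wide outcome and a narrower list.

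A reader might also infer three stronger claims, none of which the article supports.

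- **That the plan scores such a patient as having stopped.** No scoring rule is given, and a condensed article may leave that rule to the full protocol or analysis plan. The text supports only this: if Table 1 is exhaustive, the patient would not be identified as treated and could be counted as non-adherent.
- **That every other lipid product is lost.** C10AX is a residual row and takes in part of the rest. Under Study design and setting, patients not already on a statin are prescribed one before surgery, and statins are C10AA. Anyone who keeps a listed product and adds another is still captured. Only complete replacement by an unlisted product, or sole use of one from the start, matters.
- **That the error works against the intervention arm.** More intensification of lipid treatment in that arm is not established. The programme has no mandatory interventions (Self-care plan), both arms receive guideline-directed care, and the standard visits include a review of medication (Standard care programme). The direction of any difference is unknown.

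**Conclusion.** The point holds in a limited form. The primary outcome names the lipid class without restriction, while the codes cited to identify it cover three subgroups and no combination group. The consequence is conditional on Table 1 being exhaustive, on participants using an unlisted product as their only lipid treatment, and on those participants being scored by the listed codes alone.

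The result is a probably small and probably non-differential misclassification risk. With an equal loss of 1–2% of adherent patients, power falls from 0.80 to 0.79–0.78. It takes a loss of 10% to bring it to 0.70. These shares are assumptions, and the power figures also assume 1:1 allocation and 93 evaluable patients per arm. The one-arm figures should not be read as expected. The planned 186 is correct for its stated inputs and need not change. The case for acting is that the correction is almost free and is best made before the registry data are analysed.

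**What to change.** - Retrieve and score the lipid component of the primary outcome at parent level: every dispensed item under C10, including combinations.
- State that a switch from one product to another within the class counts as continued cover.
- Keep the Table 1 subgroups for describing which products were used.
- Widening the antithrombotic codes to all of B01A is optional, since no specific antithrombotic gap was shown.

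If the narrower list was intended, the alternative is to say that the lipid component is limited to the three listed subgroups and how a switch to an unlisted product is scored. That removes the contradiction but leaves the possible misclassification.

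**Cost.** One changed line in the registry request and code list, and one sentence on switching. It needs no new data source, no patient contact and no change to the sample size. Trial status reports recruitment complete and data collection ongoing, and the registry data are described as still to be retrieved. If an extract has already been taken on the Table 1 codes, the cost is a repeat request. If nothing is dispensed outside the listed codes, the results do not change.

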### Assessment of long-term risk for cardiovascular events

The Framingham Risk Score (FRS) [32] will be used to calculate the predicted 10-year risk of cardiovascular and cerebrovascular events. FRS sex-specific prediction formulas are based on general cardiovascular risk factors (age, systolic blood pressure, treatment for hypertension, smoking status, diabetes, and total and high-density cholesterol levels). The FRS will be combined with the ABI, which have been shown to improve the accuracy of risk prediction [33].

### Clinical assessments

Resting blood pressure, weight, height, calculation of body mass index (BMI), and waist circumference will be measured at study enrolment and at 1 year after revascularisation. The patients will also be asked to state their perceived pain-free walking distance.

ABI, defined as the ratio of systolic blood pressure at the ankle and systolic blood pressure in the upper arm, will be measured and calculated at study enrolment, after 4–8 weeks, and at 1 year after revascularisation.

Graft patency will be assessed using the ABI and the patients’ history. If there are any indications of re-occlusion, a Duplex ultrasound examination will be performed.

### Questionnaires

*Beliefs about medication* (BMQ) will be measured by the BMQ questionnaire [34]. This questionnaire consists of two parts, which are the BMQ-General and BMQ-Specific. The BMQ-General comprises three four-item scales assessing general beliefs about pharmaceuticals as a form of treatment. The General Harm scale assesses beliefs about the degree to which medicines are essentially harmful. The General Overuse scale assesses beliefs about whether doctors place too much emphasis and trust on medicines. The General Benefit scale assesses beliefs about the degree to which medicines are fundamentally beneficial. The BMQ-Specific comprises two scales assessing beliefs about the necessity of a specific treatment for controlling an illness (5 items) and concerns about potential adverse consequences of taking it (6 items). Each item has a five-point response scale (1 = strongly disagree to 5 = strongly agree). The validity of this questionnaire has previously been confirmed [34, 35]. Agreement to use the BMQ questionnaire has been obtained from [name].

*Health literacy* (HL) will be measured using the Swedish version of the European Health Literacy questionnaire, HLS-EU-Q16 [36]. The short version of this questionnaire consists of 16 items. These items focus on four HL dimensions reflecting perceived ease or difficulty in an individual’s ability to accessing/obtaining health information, understanding health information (not only in written form), processing/appraising health information, and applying/using health information. Response choices are “very easy”, “easy”, “difficult”, and “very difficult” [36].

*HRQoL* will be measured using the Swedish versions of EQ-5D 5 L [37, 38] and the Vascular Quality of Life Questionnaire (VascuQol-6) [39]. The EQ-5D 5 L is a generic instrument from the EuroQol Group [40] and measures health in five dimensions (mobility, self-care, usual activities, pain/discomfort, and anxiety/depression). Each dimension has five levels of severity (no problems, slight problems, moderate problems, severe problems, and extreme problems). This questionnaire includes EQ-VAS, where the participant grades their own perceived health status on a visual analogue thermometer scale with endpoints of 0–100 (0 = the worst health you can imagine and 100 = the best health you can imagine) [37]. VascuQoL-6 is a disease-specific instrument and consists of six items (symptom, pain, social life, emotional, and two items in activity) and each item has a four-point response scale [39]. Previous studies have shown that VascuQol-6 is a valid and reliable instrument for assessing HRQoL in patients with PAD [41].

The *General Self Efficacy* (GSE) scale measures people’s beliefs in their abilities to cope with a variety of difficult demands in life. The GSE scale consists of 10 items rated on a four-point Likert scale (1 = not at all true, 2 = hardly true, 3 = moderately true, and 4 = exactly true), yielding a total score between 10 and 40. The GSE scale was originally developed in Germany [42] and has been validated in Swedish [43].

*Patient-experienced quality of care* will be measured by using the questionnaire Quality from the Patient’s Perspective (QPP) [44]. In QPP, the items are evaluated by the respondent in two ways. To measure the subjective importance that the person ascribes to the various aspects of care, each item is related to the statement “This is how important it was to me …” . A four-point response scale ranging from 1 (of little or no importance) to 4 (of the very highest importance) is used for all items. To measure the perceived reality of the quality of care, each item is related to the sentence “This is what I experienced …” . In this part of QPP, a four-point response scale ranging from 1 (do not agree at all) to 4 (completely agree) is used. The short version of QPP will be used in the study [45]. The validity of QPP has been tested previously [44, 45].

*A screening instrument of unhealthy lifestyle habits* from the Swedish National Board of Health and Welfare’s National Guidelines for Methods of Preventing Disease will be used when establishing the self-care plan with the participants in the intervention group and during the follow-up sessions. This instrument includes items on tobacco use, alcohol intake, physical activity, and eating habits [11].

### Data management

All electronic study data will be stored in a password-protected local database and participants will only be identifiable by their study number. All paperwork will be kept in a locked filing cabinet in a locked office.

### Statistical analysis

Descriptive statistics will be used to describe baseline demographic and clinical data. Continuous variables will be summarised as mean (SD) or median (interquartile range), and categorical variables will be summarised as number (percentage). Comparisons between the intervention group and the control group will be made using the t-test and ANOVA for repeated measures, or the Wilcoxon rank-signed test and Kruskall–Wallis test according to the underlying distribution for continuous data. The chi-square or Fischer’s exact test will be used for categorical data. Logistic regression analysis will be performed for binary outcomes to adjust for confounding factors. All analyses will be performed according to the intention-to-treat principle. IBM SPSS version 23 or later (IBM Corp., Armonk, NY, USA) will be used for statistical analyses. The CONSORT 2010 statement will be followed when reporting the results [46].

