### Recruitment

Patients who are eligible for the study are identified by one of the study nurses at each of the two outpatient clinics. Written information about the FASTIC study, including a consent form, is sent by mail to the eligible patients. When the patients arrive to the vascular surgical ward prior to surgery, the study nurse provides oral information about the study and asks for participation. If consent is obtained, baseline data are collected. The surgery is performed and randomisation to either an intervention programme (intervention group) or a standard care programme (control group) is performed immediately after surgery by a study nurse. In some cases, the endovascular procedure may not result in revascularisation. The patient can still be randomised to the FASTIC study if a decision is made to reschedule to open surgery. If no further surgical interventions are planned, the patient will be withdrawn from the study. Figure 1 shows a description of the study flow. A time schedule of study enrolment, interventions, and assessments is shown in Fig. 2.

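### Continuous secondary outcomes that have an enrolment value are to be compared without adjusting for it: valid under randomisation, but less precise than ANCOVA

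*Protocol article*

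**What the plan says.** The Statistical analysis section of the protocol article sets the method for continuous outcomes: "Comparisons between the intervention group and the control group will be made using the t-test and ANOVA for repeated measures". It then gives a rank-based alternative for data that are not normally distributed. None of these tests carries a baseline covariate. The only adjustment named is for another type of outcome: "Logistic regression analysis will be performed for binary outcomes to adjust for confounding factors".

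The enrolment values needed for adjustment are collected:

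- Biomarkers section, covering HbA1c and lipids: "Biomarkers will be measured at study enrolment and at 1 year after revascularisation".
- Clinical assessments section, which treats blood pressure, weight, height and BMI in the same sentence: "waist circumference will be measured at study enrolment and at 1 year after revascularisation".
- Clinical assessments section, on ABI: "will be measured and calculated at study enrolment, after 4–8 weeks, and at 1 year after revascularisation".
- Recruitment section: "If consent is obtained, baseline data are collected". Surgery follows, and randomisation takes place after surgery, so these values precede allocation.

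**The concern.** A value taken before randomisation cannot be affected by the programme, and it often predicts the 1-year value. The planned tests either ignore it or use it inefficiently:

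- A t-test on 1-year values discards it.
- A t-test on change, which for two visits is the same test as the group-by-time term of a repeated-measures ANOVA, subtracts it in full whatever the correlation.
- The group main effect of a repeated-measures ANOVA averages it into the outcome, at a time when no treatment effect can exist.

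The article does not say whether the t-test is on 1-year values or on change, or which ANOVA term is the treatment test. At stake is the precision of the secondary comparisons. These include the predicted 10-year risk, which forms part of the hypothesis and of the primary objective and whose blood pressure and cholesterol inputs are measured on both occasions. Recruitment ended in November 2018, so precision can now come only from the analysis.

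**Working it through.** **The plan's own figure.** Adherence of 50% against 70%, two-sided 5%, 80% power, 1:1 allocation and no continuity correction gives 93 per arm, or 186 in total, as stated in the Sample size section. With 10% drop-out, 186 / 0.9 = 207, so 210 is enough (210 × 0.9 = 189). This concerns the binary primary outcome; it only supplies the 93 per arm used below.

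**Assumptions.** 1:1 allocation (the ratio is not stated), equal SDs in both arms and at both times, and a correlation r between enrolment and 1 year of 0.3 to 0.7 (not in the documents). No secondary outcome has a stated effect size, so the reference is the effect that gives a 1-year t-test 80% power: d = (1.960 + 0.842) × √(2/93) = 0.411 SD.

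**Variance v of the treatment contrast, relative to the 1-year t-test:**

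- 1-year t-test: 1
- change score, or group-by-time with two visits: 2(1 − r)
- ANCOVA: 1 − r²

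Power = Φ(2.8016/√v − 1.960).

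| | r = 0.3 | r = 0.5 | r = 0.7 |
|---|---|---|---|
| v, change score | 1.40 | 1.00 | 0.60 |
| v, ANCOVA | 0.91 | 0.75 | 0.51 |
| Power, 1-year t-test | 80% | 80% | 80% |
| Power, change score or group-by-time | 65.8% | 80.0% | 95.1% |
| Power, ANCOVA | 83.6% | 89.9% | 97.5% |
| Total N for ANCOVA to reach 80% (186 × v) | 169 | 140 | 95 |

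Example, ANCOVA at r = 0.5: 2.8016/√0.75 − 1.960 = 1.275, and Φ(1.275) = 0.899.

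ANCOVA has the smallest variance at every r between 0 and 1, because 1 − r² is below 1 and (1 − r²) / [2(1 − r)] = (1 + r)/2 is also below 1. The order of the other two depends on r: change is worse than the t-test at 0.3 and better at 0.7.

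**Group main effect with two visits.** It compares the arms on (enrolment + 1-year)/2. The expected difference at enrolment is zero, so it estimates (0 + d)/2, half the 1-year effect. For ABI, with three visits, the fraction would also depend on the effect at 4–8 weeks.

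**Simulation** (4,000 trials at each r, 93 per arm, true effect 0.411): ANCOVA power was 82.8%, 89.5% and 97.3%, and the group main effect averaged 0.203 to 0.207.

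**The case against.** The strongest defence is that nothing here is invalid. Allocation is randomised, so a 1-year t-test and a group-by-time test are unbiased with correct type I error, and only secondary outcomes are concerned. That stands. The article is also condensed, and a fuller analysis plan may settle which t-test and which ANOVA term is meant. That stands for those details, but the article does name the tests, and none of them adjusts for baseline.

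The gain depends on a correlation that the documents do not give. Enrolment precedes revascularisation, which could weaken the correlation for ABI. At r = 0.3 the gain over the t-test is under 4 percentage points of power, and at r = 0.7 the gain over change is about 2.4 points. Questionnaire timing is in a figure not shown, so the point is confirmed only for biomarkers and clinical measures.

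Three stronger readings are tempting but not supported:

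- **The plan dilutes the treatment effect.** Under the assumptions above, the group main effect would have only 41%, 37% and 33% power at r = 0.3, 0.5 and 0.7. The article does not say that this term will be read, and the other options are not diluted.
- **Complete-case ANOVA would leave about 170 of 210 patients for ABI.** That applies a 10% loss at each of two follow-ups (0.9 × 0.9 × 210 = 170). The Sample size section gives 10% for the trial as a whole, which leaves about 189.
- **The planned tests breach the statement "All analyses will be performed according to the intention-to-treat principle".** For two-visit outcomes, ANCOVA also needs the 1-year value, so it repairs nothing in that respect. Only ABI, with an intermediate visit, gains from a model that uses incomplete series.

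**Conclusion.** The concern holds as one of efficiency. The article fixes unadjusted comparisons for continuous outcomes whose enrolment values are already collected before randomisation. Compared with the t-test, ANCOVA lowers the variance by 9%, 25% and 49% at r = 0.3, 0.5 and 0.7; compared with the change score, by 35%, 25% and 15%. Because it is best across the range, r need not be known in order to choose it.

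These figures rest on equal SDs, 1:1 allocation and assumed correlations. Equal allocation matters: for ANCOVA without an arm-by-baseline interaction, it is what assures that precision is never worse in large samples. The 80% reference power is a yardstick, not a claim about any particular outcome. Neither bias nor type I error is at issue, and the primary outcome and its sample size are unaffected. The change is worth making, but the trial's validity does not depend on it.

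**What to change.** For each continuous secondary outcome with an enrolment value, make the main analysis an ANCOVA of the 1-year value on arm and enrolment value (site may be added), and report the adjusted mean difference with its 95% CI.

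For ABI, use a linear mixed model with all available follow-up visits, the enrolment value as covariate (or arms constrained equal at enrolment), and the 1-year contrast as the estimate. Its benefit for incomplete series applies to ABI only.

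State that the repeated-measures group main effect is not a treatment test. If an analysis plan already specifies baseline adjustment, bring the two texts into line.

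The cost is a change of wording and slightly more programming. No new data are needed, and both models are available in the SPSS package that the article names.
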